#### Evaluation

The diagnostic ML model will be evaluated using balanced classification metrics including AUROC, area under the precision-recall curve, balanced accuracy, precision, recall (sensitivity), *F*_1_-score, and specificity. Performance and CIs will be derived through Monte Carlo cross-validation, with each data split consisting of 300 participants in the training set, 50 participants in the validation set, and 50 participants in the test set. All splits will contain a balance with respect to the 5 diagnostic classes, age, gender, race, and ethnicity.

To evaluate the effectiveness of the active learning querying system, we will run post hoc simulations comparing the random selection of new data against targeted requests using active learning. We will train the classification system with 12 sessions of data, hold out the remaining 9 sessions, and plot the performance of each metric against the number of additional samples acquired using both active learning and random selection of data segments.

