#### Participant Recruitment and Management

We plan to recruit a total of 400 study participants, comprising 100 individuals formally diagnosed with ADHD, another 100 diagnosed with ASD, a further 100 diagnosed with both ASD and ADHD, and 100 individuals evaluated and confirmed to not have any socially related psychiatric conditions. Our inclusion criteria are as follows: (1) adolescents aged between 14 and 18 (inclusive) years and (2) formally evaluated for ADHD and ASD by a licensed clinician with available documentation. The selection of the final 400 participants that comprise our core data set will be based on the personal information that participants are asked to disclose. Such metadata will be used to ensure a data set that is balanced with respect to race, ethnicity, and gender. The number of participants is based on testing the ability of our system to discriminate between groups of participants. As these groups are balanced, we set the prevalence for binary classification between each condition to 50%. Following a CI of 95%, an estimated theta of 95% [42,48,49], and a width of 15%, the sample size to compute the area under the receiver operating characteristic curve (AUROC) should be 37 [54]. Considering that we have 400 participants, with 100 participants per group, this enables us to follow a common 60:20:20 (train, validation and test ratio respectively) randomized split on the data. That is, we have a sample size (test set) of 40 participants to verify the system’s ability to discriminate between the neurotypical participants and the participants who were diagnosed with either ASD, ADHD, or comorbid ASD and ADHD.

Although formal and well-established methods to perform power calculations for ML analyses have yet to be established, most digital diagnostics studies for conditions such as ASD include <100 participants per class in binary classification [47]. We aim to maintain a similar sample size per diagnostic category. The digital social experiences will be delivered to study participants for 15 minutes each day for a 3-week duration, with a single game out of the 7 possible delivered each day. At least 3 distinct 15-minute sessions will be collected per game for each participant, allowing for comparisons across days for analysis of within-peer consistency.

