**Figure 2 figure2:**
[figure not shown]
Feature extraction and quantification of behaviors relevant to neuropsychiatric diagnostics. LSTM: Long Short-Term Memory network.

For complex social features beyond the scope of automated ML-powered computational processing, we will deploy a novel crowdsourcing framework consisting of a crowd worker profiling phase, followed by a study data tagging step. In the first phase, we will post 20 tasks on Amazon Mechanical Turk, each presenting a video acquired through pilot testing of the gamified social data collection platform, followed by a series of multiple-choice questions corresponding to items from the diagnostic criteria for ADHD and ASD, as defined by the DSM-5. Each task will correspond to a separate video, and there will be 4 videos per diagnostic category used to quantify worker abilities. Worker responses will be compared against the Clinical Global Impression gold standard ratings provided by our collaborators in the Department of Psychiatry at the University of Hawai‘i. Crowd workers who align with the ratings of clinical experts on at least 1 behavioral feature, where alignment is defined as <1 categorical ordinal deviation per 2 videos, will be recruited to label the final study data from 400 participants. Recruited workers will only label those features for which their alignment with clinicians was demonstrated during the profiling phase as shown in Figure 3.

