When verifying the automatically extracted computational features manually, it is possible that some features will be incorrect. Computational feature extraction approaches are not perfect and are not necessarily robust to unforeseen conditions (eg, dim lighting, obfuscation of certain body parts, and unfamiliar accents). If any feature is consistently unreliable across several participants, then we will remove that feature from the study. There are sufficient features available, so if some do not function as intended, the study can still proceed.

It is possible that the large number of features used to train the DL classification models will be overfitted to the training set, as a data set of 400 samples (of which approximately 300/400, 75% would be in the training set) is relatively small for ML and is unlikely to capture all the intricacies of social behavior that can be expressed with the feature space. If this happens, we will run feature selection and dimensionality reduction algorithms to reduce the number of features used in the model to a minimum viable set and to summarize the feature space in a low-dimensional manner, respectively. The feature selection will enable interrogations into which features are most useful in the differentiation of each condition.

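### The evaluation splits (300/50/50 over 5 classes) contradict the 60:20:20 split of 4 groups behind the sample size; for the group-versus-group comparisons that the sample size names, a test set of 50 gives about 25 participants against the 37 required.

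*Protocol article*

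**What the plan says.** **Sample size** (Participant Recruitment and Management). Four groups of 100 are recruited: ADHD, ASD, both, neither. The inputs are "Following a CI of 95%, an estimated theta of 95% [42,48,49], and a width of 15" per cent, and "we set the prevalence for binary classification between each condition to 50" per cent. From these, "the sample size to compute the area under the receiver operating characteristic curve (AUROC) should be 37". With 400 participants, "this enables us to follow a common 60:20:20 (train, validation and test ratio respectively) randomized split on the data". The section then gives the test set as 40 participants for discriminating neurotypical participants from those with ASD, ADHD or both.

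**Model evaluation** (Multicondition Diagnostics With Adaptive Input Querying, Evaluation). Performance and CIs come from Monte Carlo cross-validation, each split having "300 participants in the training set, 50 participants in the validation set, and 50 participants in the test set". It adds: "All splits will contain a balance with respect to the 5 diagnostic classes, age, gender, race, and ethnicity".

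**Limitations.** The training share is repeated for the 400 samples: "of which approximately 300/400, 75% would be in the training set".

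**Number of classes elsewhere.** Related Work limits the output space to 4. The Methods Overview, the recruitment section and the model Description each list the same four outcomes. The model Description also says that separate binary classifiers will be built for ASD and for ADHD.

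**Worker profiling** (Novel Crowd-Powered and Traditional ML-Based Feature Extraction, Description). There are 20 tasks with one video each, and "there will be 4 videos per diagnostic category used to quantify worker abilities".

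**The concern.** The article gives two different splits and two different class counts for the same evaluation. The split fixes how many people train each model and how many test it, so it decides whether the sample-size argument describes the analysis that will be run.

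That argument rests on having at least 37 people in the test set for a comparison at 50% prevalence. If the smaller test set is the one used, the stated precision no longer follows for the comparisons that the argument names. A class count of 5 also leaves it unclear what the splits are balanced on, because no fifth group is recruited.

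**Working it through.** **1. Inputs.** From the recruitment section: AUROC A = 0.95, 95% confidence, full width 0.15, prevalence 50%, 4 groups of 100. From the evaluation section: 300/50/50.

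**2. Formula.** The article does not print its formula. The Hanley-McNeil standard error is used here:

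SE = √{[A(1−A) + (n₁−1)(Q₁−A²) + (n₂−1)(Q₂−A²)] / (n₁n₂)}, with Q₁ = A/(2−A) and Q₂ = 2A²/(1+A); width = 2 × 1.96 × SE.

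At A = 0.95: A(1−A) = 0.0475; Q₁−A² = 0.90476 − 0.9025 = 0.00226; Q₂−A² = 0.92564 − 0.9025 = 0.02314. The last two sum to 0.02540.

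**3. Reproducing the 37.** With n₁ = n₂ = N/2:

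- N = 36: √[(0.0475 + 17 × 0.02540)/324] = 0.0385, width 0.151.
- N = 37: √[(0.0475 + 17.5 × 0.02540)/342.25] = 0.0379, width 0.149.

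So 37 reproduces. It is the total for one balanced two-group comparison, with 0.15 as the full width. Read as a half-width, 0.15 would need only 11.

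**4. What the 40 must mean.** 20% of 400 is 80 tested, or 20 per group. A test set of 40 is therefore two groups, 20 + 20, so the section counts per pair of groups. Width at 20 v 20: √[(0.0475 + 19 × 0.02540)/400] = 0.0364, giving 0.143. The requirement is met.

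**5. The split in the evaluation section.** 300/50/50 is 75 : 12.5 : 12.5. Over 4 groups, 50/4 = 12.5, so 12 or 13 per group and about 25 per pair. Width at 12.5 v 12.5: √[(0.0475 + 11.5 × 0.02540)/156.25] = 0.0466, giving 0.183.

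| Test participants in the comparison | Width | 37 reached? |
|---|---|---|
| 40 (60:20:20, two groups) | 0.143 | yes |
| 37 (stated requirement) | 0.149 | yes |
| 26 (13 v 13) | 0.179 | no |
| 25 (average under 300/50/50) | 0.183 | no |
| 24 (12 v 12) | 0.187 | no |
| 20 (10 v 10, if there were 5 classes) | 0.206 | no |
| 50 (25 v 25, ASD yes/no or ADHD yes/no) | 0.127 | yes |

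**6. Why the last row differs.** Two of the four groups have ASD and two do not, and the same holds for ADHD. Each of these classifiers therefore uses the whole test set at 50% prevalence: √[(0.0475 + 24 × 0.02540)/625] = 0.0324, width 0.127.

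**7. Sensitivity to the formula.** The Newcombe variant also gives 37. The Obuchowski binormal variant gives 44, so it is not the source of the 37. Under it the width is 0.199 at 25 and 0.140 at 50. The pattern is the same: the pairs miss 0.15 and the yes/no classifiers meet it.

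**8. Profiling videos.** 20 videos at 4 per category is 5 categories; 4 categories would take 5 videos each.

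**The case against.** A reader might infer that the plan simply fails its requirement of 37. The article does not support that: each test set has 50 people. The evaluation section names no pairwise AUROCs, and the classifiers in the model Description use all 50 and reach 0.127. This stands and limits the point. The shortfall belongs to the two-group comparisons in the sample-size paragraph, whose 40 makes sense only as 20 + 20. Pooling the three diagnostic groups against the neurotypical group does not rescue that paragraph: 60:20:20 would then give 80, not 40, and prevalence would be 75% rather than 50%.

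A reader might also infer that the reported intervals will be wider than 0.15. That is not shown. The intervals come from repeated random splits, and 0.183 is the expected width for one test set of 25. Repetition does not enlarge any single test set, and the 37 was set for a test set. What is established is that the single-test-set justification does not describe the procedure in the evaluation section.

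Nor does it follow that class balance is out of reach. Exact equality over 4 classes is impossible with 50, but 12 or 13 per class is near balance. The same sentence asks for balance on age, gender, race and ethnicity, which can only be approximate in 50 people.

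The count of 5 and the video numbers might suggest an abandoned five-group design. The article mentions none, so the arithmetic shows a contradiction and not its origin. The videos are pilot material for screening workers and have no bearing on test-set size.

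A full protocol or analysis plan would not remove the point, because the article itself states both splits and both class counts.

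**Conclusion.** The concern holds in this form. The article contradicts itself on the split (60:20:20 in the sample-size paragraph; 300/50/50 in the evaluation section, with its 75% training share repeated under Limitations) and on the class count (4 throughout, 5 in the evaluation section).

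For neurotypical versus ASD, ADHD or both, the evaluation split gives about 25 test participants, against 37 required and 40 claimed. The expected width per split is about 0.18, against the 0.15 target and 0.143 under 60:20:20. For ASD yes/no and ADHD yes/no the target is still met, at 0.127.

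This assumes the Hanley-McNeil formula, which reproduces the 37, a true AUROC of 0.95, near-equal groups in each test set, and precision judged on a single split, as the sample-size paragraph does.

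**What to change.** In the evaluation section, change the number of diagnostic classes from 5 to 4. Then state one split in the recruitment section, the evaluation section and Limitations. There are two ways:

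- **Adopt 240/80/80** (60/20/20 per class) in the evaluation section, and change the training share in Limitations to 240/400 (60%). Each two-group comparison then has 40 test participants. The cost is 60 fewer training participants per split, which adds to the overfitting risk that Limitations already raises at 300.
- **Keep 300/50/50** and rewrite the sample-size paragraph. Either give the two-group precision as about 0.18 per split, or name the ASD yes/no and ADHD yes/no classifiers as the comparisons to which 37 applies (width about 0.13). The cost is either a weaker precision statement or giving up the two-group comparisons as the basis for the sample size.

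The choice is a trade-off between training size and test precision; the article needs to make it once. Both are changes of wording and need no further recruitment.

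As a separate minor correction, reconcile the 20 profiling videos with 4 categories, which means 5 per category.

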## Methods

### Overview

In contrast to prior inspirational National Institutes of Health–funded efforts and others like them, we propose an approach to digital phenotyping that expands the possible feature vectors used to classify psychiatric conditions with complex and nuanced social features that only humans can identify using a novel *crowd-powered precision diagnostics* approach. The primary high-risk and high-reward differentiators from prior work are (1) the incorporation of a novel crowdsourcing pipeline into a precision diagnostic system to enable quantification of more complex social features, (2) the adaptive querying of the participant in question within a 2-player game-based system using active learning algorithms that exploit crowdsourced responses, and (3) the differential diagnosis of ASD and ADHD simultaneously. Differentiators (2) and (3) would not be possible without (1). The addition of targeted crowdsourcing into the diagnostic process creates several technical challenges that we will address, including automating the preservation of privacy of participants, efficiently and intelligently quantifying the behavioral feature–tagging ability of crowd workers, and creating algorithms for dynamically assigning workers to new data streams and tasks. Although prior projects have attained successful performances >90% using purely automated DL approaches to differentiate ASD from neurotypical peers [47], our preliminary data show that human-in-the-loop crowdsourced feature tagging of targeted behavioral features results in classification sensitivity, specificity, and accuracy >95%, even when privacy-preserving alternations are made to the video streams [42,48,49]. We hypothesize that incorporating both human observations, which are beyond the current and foreseeable abilities of ML, into the feature extraction process will provide enough social information for automated models to classify each condition using the same video data.

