To model the multilabel classification problem, we will create separate binary classifiers for ASD and ADHD. Each model will be optimized separately. In comparison with training distinct binary classifiers, a single model trained in a multitask learning setup is able to share parameters between the classification tasks. This helps the model focus on distinguishing features between conditions and has been found to reduce overfitting. We expect that the multitask setting will decrease the number of false-positive predictions by helping the model recognize features that overlap between conditions.

Using a sigmoid activation function for each independent classifier, the classification system will output a probability score for each diagnostic possibility as well as each of the behaviors defined by the DSM-5, which will be quantified by the system.

Using the output scores of the DL model, an active learning system will be developed that queries for additional data from the user in a targeted manner by suggesting the next game for the participant to play. For each participant, the algorithm will measure the confidence score of each behavioral symptom and produce a list of games for the user to play, sorted by the classifier’s mean uncertainty of the behavioral symptoms each game is designed to curate data for. Classifier uncertainty will be measured by the entropy of each classifier’s output vector. As neural networks are inherently uncalibrated, we will apply a method published by Kuleshov et al [60] based on isotonic regression to calibrate the probability estimates before measuring uncertainty.

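### Comparing adaptive querying with random selection alone cannot show that adapting to the individual participant adds anything

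*Protocol article*

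**What the plan says.** The comparison is set out in the protocol article, Methods, Multicondition Diagnostics With Adaptive Input Querying, Evaluation: "we will run post hoc simulations comparing the random selection of new data against targeted requests using active learning". The set-up is "We will train the classification system with 12 sessions of data, hold out the remaining 9 sessions", and the output is to "plot the performance of each metric against the number of additional samples acquired using both active learning and random selection of data segments". Random selection is the only reference named for the querying system anywhere in the article.

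The system itself is described as individual. The Description in the same section says: "For each participant, the algorithm will measure the confidence score of each behavioral symptom and produce a list of games for the user to play". Games are ordered by the classifier's "mean uncertainty of the behavioral symptoms each game is designed to curate data for". The Methods Overview lists among three main differentiators from prior work "the adaptive querying of the participant in question within a 2-player game-based system using active learning algorithms that exploit crowdsourced responses".

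The sessions come from the schedule in Participant Recruitment and Management: "15 minutes each day for a 3-week duration, with a single game out of the 7 possible delivered each day", and "At least 3 distinct 15-minute sessions will be collected per game for each participant".

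**The concern.** A gain of active learning over random selection can have two sources. Some games may be more informative for everybody, so that any sensible ranking picks them early. Or the most useful next game may differ between participants, and the system finds it. Only the second is adaptation to the participant.

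The article makes the first source plausible without measuring it. Table 2 gives the games different target behaviors. The Results report that three feature selection methods agreed on a set of behaviors at population level, and the games are to be modified to target these. A ranking by mean uncertainty could therefore favor much the same games for most participants.

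At stake is what may be concluded about a stated differentiator. If a common order did as well, the per-participant choice of the next game would not be needed.

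**Working it through.** **The plan's own figures.** 3 weeks × 7 days = 21 sessions; 7 games × 3 sessions = 21; 12 used + 9 held out = 21. The set-up is internally consistent, so the issue is only the choice of reference.

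**What the comparison identifies.** At any number of added sessions,

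(active − random) = (fixed order − random) + (active − fixed order).

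The planned curves give the left side only. The claim about adaptation concerns the last term.

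**Illustrative simulation.** The article gives no noise or information per game, so every game parameter here is an assumption.
- 40,000 virtual participants, 7 games, 3 sessions each; 12 sessions drawn at random are known, and 9 are added one at a time.
- Symptom for game g: s_g ~ N(0, 1). Session value: s_g + N(0, sd_g²), with sd_g = 1.5·exp(h·Z) and Z standard normal, drawn per participant and game. The value h sets how much noise differs between participants.
- Diagnosis: positive if Σ w_g·s_g > 0. Weights are equal, or proportional to 2.5, 1.8, 1.2, 0.7, 0.4, 0.2, 0.1.
- Score: Σ w_g × posterior mean of s_g.
- Random: any remaining session. Fixed: highest w_g² first, the same for all. Adaptive: largest w_g²·(v_n − v_(n+1)), where v_n = 1/(1 + n/sd_g²) and n is the number of sessions of that game already seen.

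Mean AUROC over added sessions 1 to 8:

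| Games | h | Random | Fixed | Adaptive | Adaptive − random | Fixed − random | Adaptive − fixed |
|---|---|---|---|---|---|---|---|
| Unequal | 0 | 0.8337 | 0.8505 | 0.8507 | 0.0170 | 0.0168 | 0.0002 |
| Unequal | 0.5 | 0.8336 | 0.8477 | 0.8482 | 0.0146 | 0.0141 | 0.0005 |
| Unequal | 1.0 | 0.8343 | 0.8450 | 0.8462 | 0.0119 | 0.0107 | 0.0012 |
| Equal | 0 | 0.8325 | 0.8319 | 0.8353 | 0.0028 | −0.0006 | 0.0034 |
| Equal | 0.5 | 0.8323 | 0.8316 | 0.8366 | 0.0043 | −0.0007 | 0.0050 |
| Equal | 1.0 | 0.8331 | 0.8322 | 0.8393 | 0.0062 | −0.0009 | 0.0071 |

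**Reading.** With unequal games the common order accounts for 0.0168/0.0170 = 99%, 0.0141/0.0146 = 97% and 0.0107/0.0119 = 90% of the gain over random. With equal games it accounts for none. The adaptive rule beats random in all six rows, and by more (0.0119 to 0.0170 against 0.0028 to 0.0062) in the rows where adapting contributes least. The size of the win over random is therefore no guide to the value of adaptation; the last column is.

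**End points.** All three curves coincide before any session is added and again after all 9. For unequal games with h = 0, each starts at 0.799 and ends at 0.859. Only intermediate numbers of sessions carry information.

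**Limits of the simulation.** The adaptive rule is idealized, with known weights and noise, and is not the entropy ranking of the article. The fixed order also uses the true weights. With equal games it has nothing to rank by, and ties were broken at random. In the row with equal games and h = 0, the adaptive gain comes only from filling in games seen less often among the first 12 sessions. One random seed was used, so the smallest differences should not be read closely.

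**The case against.** Random selection is a reasonable lower baseline, and it answers the question the Evaluation literally asks, whether targeted requests beat untargeted ones. The article's explicit hypothesis concerns combined versus single-source features; nowhere does it state that an individual order beats a common one. The comparison is a secondary, post hoc simulation and leaves the diagnostic accuracy analysis untouched. All of this stands and limits the weight of the point. It does not remove the point, because the querying is described as individual throughout, and because the comparator is named rather than left to a fuller document.

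Three stronger readings are tempting, and the article does not support them:
- A reader might infer that a fixed list of games would necessarily win too. That holds only if the games differ in average information, which the article does not quantify.
- A reader might infer a false-positive rate. In a second simulation, adaptation had no value by construction and 2 of 7 games were assumed both noisier and more diagnostic. A one-sided 5% paired test preferred active to random in 38–93% of runs with 400 scored participants and 15–48% with 80. The rate fell to 3–6% with equally informative games and 0–2% when the noisier games were not diagnostic. These are not error rates for this study: the article plans curves and no such test, its test sets hold 50 participants, and in the 38–93% settings active selection really was better than random (AUROC 0.877–0.943 against 0.868–0.923).
- A reader might infer that a fixed order would do away with the model and the crowd ratings. Both are still needed for the diagnosis; only the per-participant choice of game would be saved.

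**Conclusion.** The concern holds as a gap in attribution. Active versus random can support the statement that targeting helps. It cannot support the statement that adapting to the participant helps, because a difference in average game quality produces the same pattern and no other planned comparison separates the two. Under the assumed parameters the share of the gain explained by a common order ranges from none (equal games) to about 99% (unequal games, no between-participant noise differences). The article does not allow a narrower range for this study. The logic of the gap does not depend on these numbers; their size does. The change is worth making because it is cheap and bears on a stated differentiator. No sample size or diagnostic accuracy result is affected.

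**What to change.** In the same post hoc simulation, on the same 9 held-out sessions, add a third curve that uses one game order for all participants. Derive that order from training participants only, for example by mean entropy or mean gain per game. Base any claim about adaptation to the participant on active versus fixed order at intermediate numbers of added sessions. Keep random selection as the lower baseline. An arm in which each participant receives another participant's ranking is an optional supplement.

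No new participants, sessions or procedures are needed, only slightly more computation. The downside is that the gain credited to adaptation may turn out smaller than the gain over random.
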